### Assessment of primary outcome

The primary outcome of the study will be patients’ recall of information as a function of physicians’ training. For detailed assessment see Table 5.

### Assessment of secondary outcomes

The secondary outcomes will be higher patient satisfaction, better adherence to medication, more adequate disease management, and reduced anxiety. For detailed assessment see Table 5.

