## Secondary Objectives

The secondary outcomes will be higher patient satisfaction,^4^ better adherence to medication,^4,5^ more adequate disease management,^6^ and reduced anxiety.

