|  | State anxiety and depression | German version of the Hospital Anxiety and Depression Scale (HADS-D),^31^ a brief instrument containing two scales of 7 items assessing state anxiety and depression. |
|  | Medical knowledge | Multiple-choice test consisting of 6 questions of increasing difficulty developed by our research team. |
| Interview | Immediate recall | Patients will be asked to freely recall all information provided immediately after the discharge event, “Can you tell me all the information your physician just provided?”, and repeated use of prompts, “Was there any other information you can recall?” until the patient cannot recall any more information. |
|  | Satisfaction | Once patients cannot recall any additional information, they will be asked to characterize their satisfaction with the discharge communication event and physician. Specifically, we will previously developed items (see Study 4) asking patients to rate on a scale from 1 to 10 the (1) physician’s comprehensibleness, (2) information structuring, and (3) willingness to recommend the physician to family and friends. |
| Telephone Interview | Delayed recall | Patients will be asked to freely recall all information mentioned in the discharge event, “Can you tell me all the information your physician provided when you left the emergency department?”, and repeated use of prompts, “Was there any other information you can recall?” until the patient cannot recall any more information. In addition, patients will be asked whether they have received additional information from their general practitioner since discharge. |
|  | Adherence to recommendations | Patients will be asked to list all the physician recommendations that they have actively pursed, “Can you tell me which of your physician’s recommendations you have pursued?”. |
|  | Overall assessment | German version of the Patient Reactions Assessment (PRA-D),^32^ composed of three 5-item scales designed to measure information, affective, and communication components of physician–patient communication. |

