### Assessment of other outcomes of interest

Basic demographic measures concerning each patient as well as a number of other measures that will serve as covariates in the analysis, such as patients’ health status, memory ability, state anxiety, state depression, and medical knowledge. The rationale for including these measures is that they are potential moderators of participants’ recall of discharge information and thus should be included in the statistical analysis. For detailed assessment see Table 5.

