## Procedures at each visit

### Pre-discharge assessment

Patients will be asked to participate in the study before they have their discharge event. If they agree to participate they will be asked about they’re demographics health-related quality of life, their memory and about their state anxiety and depression. For detailed assessment see Table 5.

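### Reduced anxiety is listed as a secondary outcome, but anxiety is measured only before the discharge communication, so no effect of that communication on anxiety can be estimated

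*Protocol*

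**What the plan says.** Two sections of the protocol make anxiety an outcome. Section 4.3 (Secondary Objectives) ends its list of secondary outcomes with "and reduced anxiety". Section 9.2.2 repeats the list: "The secondary outcomes will be higher patient satisfaction, better adherence to medication, more adequate disease management, and reduced anxiety". It also says where the measurement is described: "more adequate disease management, and reduced anxiety. For detailed assessment see Table 5".

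Table 5, in section 9.2, holds one anxiety instrument: "German version of the Hospital Anxiety and Depression Scale (HADS-D),^31^ a brief instrument containing two scales of 7 items assessing state anxiety and depression". It stands in the pre-discharge block. Section 9.3.1 places that block in time: "Patients will be asked to participate in the study before they have their discharge event". It includes questions on "their memory and about their state anxiety and depression".

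Section 9.2.3 gives the same score another role. It lists "health status, memory ability, state anxiety, state depression, and medical knowledge" as covariates, on the ground that they may moderate recall. The synopsis and sections 5.3 and 9.2 say the same.

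**The concern.** An outcome that the discharge communication is meant to change has to be measured after it. Here the section naming the outcome points to a table that measures anxiety only beforehand. A team following the schedule would finish data collection with no anxiety value from after the discharge talk. The outcome would then go unreported, or be filled with a score that cannot reflect that talk.

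The protocol itself gives anxiety weight. Section 3.1 counts lower anxiety among the benefits of good discharge communication. Section 3.8 uses anxiety to justify the choice of population. Section 3.2 gives the NURSE model used in the control training two goals: less anxiety and better compliance. Without a later anxiety measure, the trial could not show whether better recall in one arm came with more or less anxiety than in the other.

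**Working it through.** No power, effect size or sample size enters here, and the plan gives no figure to reproduce. The check sets the schedule beside the outcome lists and the analysis section.

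**Step 1: where anxiety is measured** (Table 5 and sections 9.3.1 to 9.3.3)

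| Contact | Content | Anxiety measure |
| --- | --- | --- |
| Before discharge | Demographics, SF-12, CERAD word list, HADS-D, medical knowledge | 1 |
| Immediately after discharge | Free recall, satisfaction ratings | 0 |
| Day 7 call | Delayed recall, general practitioner question, adherence, PRA-D | 0 |
| Day 30 call | As day 7 | 0 |

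Anxiety measurements after the discharge communication: 0 + 0 + 0 = 0, over three contacts.

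The PRA-D has an affective scale, so it is the one candidate for a substitute. Table 5 describes it as rating components of physician–patient communication. It does not measure the patient's state anxiety.

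**Step 2: what the outcome needs.** Write A_pre for the HADS-D anxiety score before discharge and A_post for a score at any later contact.

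- Change within patient: A_post − A_pre.
- Arm effect after discharge: mean A_post (information structuring) − mean A_post (emotion skills), with or without adjustment for A_pre.

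Both need A_post, which step 1 shows is never collected. The arms could be compared on A_pre, since physicians are trained before they see study patients. But A_pre precedes the discharge communication and cannot carry its effect.

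**Step 3: where anxiety is listed as a secondary outcome**

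| Place | Secondary outcomes listed | Anxiety? |
| --- | --- | --- |
| Synopsis | Satisfaction, medication intake, disease management | No |
| Section 4.3 | Satisfaction, adherence, disease management, anxiety | Yes |
| Section 5.2 | Satisfaction | No |
| Section 9.2.2 | Satisfaction, adherence, disease management, anxiety | Yes |

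Anxiety appears in 2 of these 4 lists. In those two it is one of four outcomes.

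**Step 4: what is planned for it.** Beyond recall, section 11.4 plans effect models for satisfaction and adherence only. Section 11.4.3 plans no secondary analyses. Anxiety enters only as a covariate.

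**The case against.** The strongest reply is that this is a drafting carry-over. The list in section 4.3 closely follows a sentence in section 3.1 and keeps most of its citation marks, and section 9.2.2 repeats it. The synopsis and section 5.2 leave anxiety out, and no analysis of it is planned. On this reading the team never meant to test anxiety, and only stray words are at fault. That is plausible, and it keeps the consequence small. It does not remove the contradiction: section 9.2.2 still names the outcome and sends the reader to a table that does not measure it after discharge.

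Three stronger readings are tempting, and the document does not support them.

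- *The control programme's main benefit goes unmeasured.* Section 3.2 gives the NURSE model two goals and does not rank them. The other, compliance, is covered in part by self-reported adherence at the calls. Section 3.6 also justifies the emotion training as a control for a general emphasis on communication. The trial's objective is the advantage of information structuring.
- *The pre-discharge score is contaminated by training and should leave the recall model.* Section 7.2 has trained physicians alert the study team when discharge is pending, so the HADS-D may follow contact with a trained physician. That such contact shifts the score is inference, and the protocol gives no figure for it. The same worry would apply to an anxiety model adjusted for that score. It is a caveat and does not justify changing the recall model.
- *The arms will be compared on the pre-discharge score as if it were an outcome.* Nothing in the protocol proposes this.

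**Conclusion.** The point holds as an internal contradiction with a practical consequence. Sections 4.3 and 9.2.2 list an outcome for which the schedule gives one measurement before the discharge communication and none at the three contacts after it. Under that schedule, no effect of the communication on anxiety can be estimated. An analysis plan, which may exist but is not shown, could not supply uncollected data.

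The size is limited: one of the four outcomes in the two sections that list it, with no model attached. Recall, its measurement and the sample size are untouched. The conclusion assumes that Table 5 and sections 9.3.1 to 9.3.3 give the full content of each contact, and that the PRA-D is not meant as an anxiety measure, as its description in Table 5 indicates.

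**What to change.** Choose one of two consistent plans.

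1. **Keep the outcome.** Add the 7-item HADS-D anxiety scale to an existing follow-up call, compare the arms on it with the pre-discharge score as covariate, and note that this score may follow contact with the trained physician. List the outcome in the same way in the synopsis and sections 4.3, 5.2 and 9.2.2, and name its model in section 11.4. The cost is a somewhat longer call. The calls are set at 5–10 minutes and already hold prompted recall, the general practitioner question, adherence and the 3 × 5 = 15 items of the PRA-D. No new contact is needed.
2. **Drop the outcome.** Delete reduced anxiety from sections 4.3 and 9.2.2 and keep the HADS-D as a covariate only. This costs a text change in two sections and brings them into line with the synopsis and section 5.2 on anxiety. The trial would then make no statement about anxiety.

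Neither plan requires a change to the recall model.

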### Assessment of other outcomes of interest

Basic demographic measures concerning each patient as well as a number of other measures that will serve as covariates in the analysis, such as patients’ health status, memory ability, state anxiety, state depression, and medical knowledge. The rationale for including these measures is that they are potential moderators of participants’ recall of discharge information and thus should be included in the statistical analysis. For detailed assessment see Table 5.

### Assessment of safety outcomes

NA

#### Adverse events

NA

#### Laboratory parameters

NA

#### Vital signs

NA

### Assessments in participants who prematurely stop the study

Data from the participants won’t be used for the study. There won’t be any disadvantages for the participant.

## Procedures at each visit

### Pre-discharge assessment

Patients will be asked to participate in the study before they have their discharge event. If they agree to participate they will be asked about they’re demographics health-related quality of life, their memory and about their state anxiety and depression. For detailed assessment see Table 5.

### Interview

After the discharge event they will be asked what they can immediately recall and about their satisfaction with the discharge event and the physician. For detailed assessment see Table 5.

### Telephone or personal interview 1&2

And in the telephone interviews (7 days and 30 days after the discharge event) they will be asked to give a delayed recall, how strictly they adhered to the recommendations and there will be an overall assessment. For detailed assessment see Table 5.

# SAFETY

## Drug studies

NA

### Definition and assessment of (serious) adverse events and other safety related events

NA

### Reporting of serious adverse events (SAE) and other safety related events

NA

### Follow up of (Serious) Adverse Events

NA

## Medical Device Category C studies

NA

### Definition and Assessment of (Serious) Adverse Events and other safety related events

NA

### Reporting of (Serious) Adverse Events and other safety related events

NA

### Follow up of (Serious) Adverse Events

NA

## Medical Device Category A studies

### Definition and Assessment of safety related events

Health hazards that require measures:

There won’t be findings in the trial that may affect the safety of study participants and which require preventive or corrective measures intended to protect the health and safety of study participants.

### Reporting of Safety related events

Reporting to Sponsor-Investigator:

Health hazard that require measures are reported to the Sponsor-Investigator within 24 hours upon becoming aware of the event:

Pregnancies:

Reporting of pregnancies is not necessary.

Reporting to Authorities:

In Category A studies it is the Investigator’s responsibility to report to the local Ethics Committee health hazards that require measures within 2 days.

# STATISTICAL METHODS

## Hypothesis

We hypothesize that patients receiving structured discharge information from their trained physicians will be able to recall more information and show higher adherence to recommendations relative to controls (i.e., patients receiving discharge information from doctors trained in emotion-handling skills). We’ll therefore collect data from 200 patients with chest pain and from 200 patients with abdominal pain during 1 year.

## Determination of Sample Size

Within three months 50 patients with chest pain and 50 patients with abdominal pain will be recruited. Including 4 groups with 100 patients this sums up in 400 patients in one year. Sample of 400 gives acceptable power of .8 for comparison of four groups for medium effect sizes of .4.

## Statistical criteria of termination of trial

We’ll stop collecting data after interviewing 400 patients.

## Planned Analyses

The evaluation of the effects of the two training programs will be conducted using mixed-effects model.^33^ Mixed-effects models are statistical models containing both fixed (e.g., intervention program) and random (e.g., patient) effects and are used in a variety of disciplines including medical and social sciences, where repeated measurements are made on the same statistical units or on clusters of related statistical units. Specifically, our analysis will take into account the fact that physicians belong to particular clusters (see Study Design) and the same physician treats several patients, by clustering physicians by training program and patients by physician. These multivariate analysis methods also allow for simultaneous statistical adjustment for covariates of interest, including patient characteristics, such as age, memory ability, and so on. Similar models will be used to estimate the effect of the training programs on patient satisfaction, and adherence to discharge recommendations.

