# STUDY DESIGN

## General study design and justification of design

The study will use a cluster randomized controlled trial. Clusters of physicians (cohorts of six physicians commencing training in a three-month period; total of four clusters in the one-year intervention period) will be assigned to one of two types of training (information-structuring skills vs. emotion-handling skills). The physicians won’t know to which cluster they belong. The primary outcome of the study will be patients’ recall of information as a function of physicians’ training. For this purpose, we aim to recruit 50 patients presenting to the emergency department with chest pain and 50 patients with abdominal pain in each three-month period (*N* = 400, in the one-year study period) and document the respective discharge communication (via audio recordings). In addition, each patient will be asked to recall the discharge information immediately after the discharge event, seven days and 30 days later (telephone interview), as well as complete a number of other measures to assess secondary outcomes, such as overall satisfaction and adherence to recommendations. The study will be conducted at the emergency department of the University Hospital of Basel (Switzerland).

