## Methods of minimising bias

### Randomisation

Clusters of physicians will be pseudo-randomly assigned to one of the two training programs (information structuring vs. emotion-handling skills training).

Table 3. Training/Interviewing Timeline for Each Cluster of Physicians (*k*)/Patients (*n*)

| Cluster | Months 1-3 | Months 4-6 | Months 7-9 | Months 10-12 |
| --- | --- | --- | --- | --- |
| 1 | Information Structuring  (*k*=6, *n* = 100) |  |  |  |
| 2 |  | Emotion Skills  (*k*=6, *n* = 100) |  |  |
| 3 |  |  | Information Structuring  (*k*=6, *n* = 100) |  |
| 4 |  |  |  | Emotion Skills  (*k*=6, *n* = 100) |

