# STUDY POPULATION

## Eligibility criteria

Inclusion:

We will train a total of 24 physicians. The intervention will be assessed by interviewing a total of 400 patients who present to the emergency department of the University Hospital Basel with chest pain or abdominal pain and who are seen by one of the study participants.

We will use the following exclusion criteria concerning patients with chest pain (see Figure 3):

- Patients *younger than 18 years of age* will not be recruited because of limited ability to provide informed consent.
- Patients with *limited ability to communicate in German* (the default language at the hospital) will not be recruited to exclude additional confounds related to language proficiency.
- Patients with *dementia* will not be recruited to avoid additional confounds arising from pathological memory deficits.
- Patients with *increased troponin level*, an indicator of myocardial infarction, will not be recruited to minimize stress on these more vulnerable patients.
- Patients with none of five *cardiovascular risk factors* (cvRF; smoking history, diabetes, hypertension, dyslipidemia, age above 50 years, or family history of coronary heart disease) will not be recruited because chest pain symptoms in such patients are typically indicative of diagnoses unrelated to coronary heart disease, requiring a very different follow-up and health management recommendations (e.g., in the case of an anxiety disorder).

*
[figure not shown]
*

Figure 3. Decision Tree for Participant Exclusion/Inclusion in the Intervention Assessment

We will use the following exclusion criteria concerning patients with abdominal pain:

- Patients *younger than 18 years of age* will not be recruited because of limited ability to provide informed consent.
- Patients with *limited ability to communicate in German* (the default language at the hospital) will not be recruited to exclude additional confounds related to language proficiency.
- Patients with *dementia* will not be recruited to avoid additional confounds arising from pathological memory deficits.

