## Assignment to study groups

The first communication skills training will be randomly assigned by *randomizer.org*. After knowing which communication skills training will be the first, the trainings will be alternately assigned.

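### The planned model promises to account for the assigned physician cohorts, but the levels it names contain no cohort term, so its error may be too small for the primary test

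*Protocol*

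**What the plan says.** The unit of assignment is the cohort. Protocol 6.2.1 states: "Clusters of physicians will be pseudo-randomly assigned to one of the two training programs". Section 6.1 describes the clusters as "cohorts of six physicians commencing training in a three-month period; total of four clusters in the one-year intervention period". The timeline table in 6.2.1 gives each cohort its own calendar quarter, with two cohorts per program. Section 7.3 draws only the first training at random: "After knowing which communication skills training will be the first, the trainings will be alternately assigned". Section 7.1 adds: "We will train a total of 24 physicians". Section 11.2 gives the patient numbers: "Including 4 groups with 100 patients this sums up in 400 patients in one year".

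On the model, section 11.4 first states the aim: "our analysis will take into account the fact that physicians belong to particular clusters (see Study Design"). It then says how this will be done: "by clustering physicians by training program and patients by physician". The synopsis entry on statistical analysis has the same text. Both places give the intervention program as their example of a fixed effect. The power simulation in the synopsis entry on number of participants uses a mixed model with patients clustered by physician and mentions no cohort.

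**The concern.** The aim and the named levels disagree. The clusters of section 6.1 are cohorts, whereas the levels in 11.4 are patient, physician and training program. Program has two values and is the contrast being tested, so it cannot also supply the between-cluster error. Followed as written, the model judges the training effect against variation between physicians only.

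The six physicians of a cohort share a place in the teaching schedule and a calendar quarter. Any difference in delivery of the training, season or case mix by quarter falls on all six together, and so on about 100 patients. A physician random effect absorbs only part of that. The p-value and interval for recall are at stake. So are those for satisfaction and adherence, for which 11.4 plans similar models.

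**Working it through.** **Inputs from the protocol.** 4 cohorts, 2 per program; 6 physicians per cohort, 12 per program; 100 patients per cohort, 200 per program, so m = 100/6 = 16.7 patients per physician. Effect size d = .59 (synopsis).

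**Assumptions.** Two-sided 5% level (not stated). Total variance 1, split into cohort share c, physician share p and residual s = 1 - c - p. The protocol gives neither c nor p, so ranges are shown. Groups are balanced.

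**1. The plan's own power.** With independent patients and SD 1, the normal approximation at d = .59 gives 98.7% with 100 per group, 83.9% with 50 and 95.1% with 75 (25% attrition). These agree with the synopsis figures of over .9 and over .8. They contain no cohort variance.

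**2. True and model variance of the difference between programs.**

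- True: 2 × (c/2 + p/12 + s/200).
- Expected from a physician-level analysis: 2 × (p + s/m + 6c/11)/12. The factor 6/11 is the part of the cohort variance that shows up between the 12 physicians of one program.

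Example with p = .05, c = .01, s = .94:

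- True = 2 × (.0050 + .0042 + .0047) = .0277.
- Model = 2 × (.0500 + .0564 + .0055)/12 = .0186.
- Ratio of standard errors = √(.0277/.0186) = 1.22.

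Over c = .01 to .05 the ratio runs from 1.22 to 1.75 at p = .05, and from 1.36 to 2.06 at p = 0.

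**3. Type I error at nominal 5%.** Simulated null trials (at least 200,000 per setting), with a t-test on physician means:

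| Cohort ICC | Physician ICC 0 | .05 | .10 |
| --- | --- | --- | --- |
| 0 | 5% | 5% | 5% |
| .01 | 14% | 10% | 9% |
| .02 | 21% | 15% | 12% |
| .05 | 33% | 25% | 21% |

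A t-test on the four cohort means stays at 5% in every cell. The 95% t multipliers are 4.30 on 2 df and 2.07 on 22 df.

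**4. Power of the cohort-level test** (noncentral t on 2 df, noncentrality = .59 divided by the true SE):

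- c = 0, p = 0: .59/√.0100 = 5.90, power 83%.
- c = .01, p = 0: .59/√.0199 = 4.18, power 60%.
- c = .01, p = .05: .59/√.0277 = 3.54, power 48%.

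**5. Would a cohort random effect be enough by itself?** In the balanced case the cohort variance is estimated as zero when the between-cohort mean square (2 df) does not exceed the between-physician mean square (20 df). At p = .05 this happens in 46%, 37% and 22% of trials for c = .01, .02 and .05. In those trials the model falls back to the physician-level error.

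**6. Time trend.** Under alternation one program has quarters 1 and 3 (mean 2) and the other has quarters 2 and 4 (mean 3). A steady trend therefore shifts the contrast by one quarter's change, whichever error term is used.

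**The case against.** The strongest reply is that this is loose wording. Section 11.4 says outright that cluster membership will be taken into account and points to the study design, where clusters are the cohorts. The timeline labels each cohort by its program, so clustering by program may be shorthand for clustering by training cohort. This stands in part: the intent is there, and the protocol should not be read as having deliberately chosen to ignore cohorts. It does not rescue the named levels, because elsewhere training program means one of two programs, no section names a cohort term, and the power simulation clusters by physician only.

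A second reply is that the harm is conditional. That stands: with no cohort variance the physician-level test holds its level.

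A reader might also infer more than the text supports:

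- **That the protocol fixes a test on 22 df.** It states no degrees of freedom. The figure follows from one reading (24 physicians less 2 groups), and the method for degrees of freedom may properly be left to the analysis plan.
- **That the error rate is known to be inflated by a given amount.** The protocol gives no intraclass correlation, so the size is a range.
- **That each cohort has its own study staff.** The document does not say so, and the point does not need it.

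**Conclusion.** The point holds as an internal contradiction with a conditional consequence. The assigned unit is the cohort, the stated aim is to account for it, and the levels written in 11.4 and the synopsis omit it. If cohort ICC is 0, nothing is lost. At assumed cohort ICCs of .01, .02 and .05, the type I error of a physician-level test is about 9-14%, 12-21% and 21-33% over physician ICC 0 to .10. These figures assume balanced groups, a two-sided 5% level, and cohort effects that are independent and exchangeable.

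The last assumption also limits the remedy. A reader might infer that a 2-df test makes the comparison safe. It restores the error rate under independent cohort effects. It does not remove bias from a trend over the year, because section 7.3 randomises only the first training and leaves two possible sequences.

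**What to change.** In section 11.4 and the synopsis, state the levels as patients within physicians within assigned cohort, with training program as the fixed effect. Make the governing primary test one against between-cohort variation: a comparison of cohort-level results on 2 df. A mixed model with a cohort random effect may accompany it, but should not govern, because with two cohorts per program it often estimates the cohort variance as zero. Label any physician-level result as assuming no cohort or period effect. State that alternation leaves the contrast open to a time trend.

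The change needs no new data, but it is more than a wording change. Intervals become wider, and the power statements in the synopsis and section 11.2 must be restated on this basis. At d = .59 with 400 patients, power on 2 df is 83% at best, with no cohort or physician variance. It is about 48-60% at cohort ICC .01 with physician ICC .05 to 0. The protocol should then either acknowledge this limit of four cohorts or plan for more.
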